**Methods:**

This prospective, randomized, controlled trial will focus on psychometric testing of attentional abilities assessed with the Attention Network Test for Child (Child ANT) and involves a mixed measurement design. Forty-eight children aged 7-years, half of whom were premature at birth and in their expected grade without learning difficulties will be included after parental consent. They will be equipped with a head-mounted display in which the Child ANT will be presented. The association of different flankers and pre-cues will allow the measurement of the development level of Alerting, Orienting, and Inhibition function. The task will be composed of one experimental block of trials randomly performed per posture: seated, standing, or free.

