To check the children’s understanding of ANT, a 12-trial practice block, lasting less than 2 min, will be executed in the seated position. The children will receive feedback on their success. After this practice block, they will execute 48 trials in each position (with a 1-min 30-s break after 24 trials): 4 cue conditions × 2 target locations (up, down) × 2 target directions (left, right) × 3 flanker conditions (neutral, congruent, incongruent). The order of the trials will be randomized. Overall, each experimental block will last less than 3 min. Between each experimental block, the children will have a 3-min break. During these breaks, they will rate the subjective dimension of their arousal based on the adapted Self-Assessment Manikin scale [45]. They will point to one of five figures on a teddy bears’ scale (Fig.2), or between any two figures, which results in a 9-point rating scale. Overall, the experiment will last about 30 min.

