### Statistical analyses

To determine the number of children to include, we relied upon Rueda et al. [12], showing a global sitting performance of an overall RT of 931 ± 42 ms in 6-years-old children born at term and 833 ± 123 ms in 7-years-old children born at term. Because children born prematurely are usually considered to have about a 1-year delay for learning abilities, we calculated that to demonstrate a catch-up related to the mobility condition, sitting being the reference, for each attention component, with an alpha risk of 0.00625 (Bonferroni correction for the number of tests) and a power of 0.80, 24 children would be needed in each group (Power and Precision™ V4, Biostat Inc., Englewood, NJ, USA 2001).

Thus, we will first compare the overall RT of the children born at term versus those born prematurely. Then, we will compare separately the mean scores (± standard deviation) obtained for each of the attention components. After having verified the required assumptions about data distributions (normality of attentional scores, homoscedasticity and sphericity), the level of each attention component will be analyzed by the means of three mixed analyses of variance, with position condition (seated, standing, free) as a within-subject factor and gestational age (children born preterm vs. children born at term) as a between-subject factor. For all analyses, post hoc tests will be conducted using Tukey’s honestly significant difference method when needed.

To evaluate the subjective arousal level of children between the positions, the Friedman test will be performed on each score on the Self-Assessment Manikin scale with position (seated, upright, and free) as a within-subject factor.

The statistical thresholds for significance will be set to 0.05 for the remaining analyses.

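### The named mixed ANOVAs, as usually run, drop a child with one missing position block; a mixed model on all completed blocks is a cheap safeguard

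*Protocol article*

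**What the plan says.** Under Statistical analyses, the article states that "the level of each attention component will be analyzed by the means of three mixed analyses of variance". Position, at three levels, varies within child, and birth group (term or preterm) varies between children. The assumptions to be verified first are "normality of attentional scores, homoscedasticity and sphericity". The sample size is set "with an alpha risk of 0.00625 (Bonferroni correction for the number of tests) and a power of 0.80", giving 24 children per group. The Abstract plans "Forty-eight children aged 7-years, half of whom were premature at birth".

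Under Design and setting of the study, each child does a practice block and then three blocks of 48 trials, one per position in random order, with breaks within and between blocks: "Overall, the experiment will last about 30 min". Under Data acquisition, scores use correct responses only, and each block is filmed and given an observation sheet to check that the position instructions were followed.

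The article does not say what happens to a child with one or two usable blocks. It gives no replacement, imputation or complete-case rule and no expected rate of incomplete sessions.

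**The concern.** A sphericity check belongs to the classical repeated-measures ANOVA, which works on a full set of three position scores per child. As usually run, it omits a child who lacks one of them, and the blocks that child did complete go unused.

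Two things are at stake. The first is efficiency, because there are no spare children to absorb a loss. The second is bias in the between-group level. The Background and Discussion describe weaker attention in children born preterm. If weak attention also makes a child more likely to stop, or to produce an unusable block, the completers in the preterm group would be a better-performing subset. The term-versus-preterm gap would then be understated, as would the distance to make up in any catch-up judged against that gap.

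**Working it through.** **1. The plan's own sample size.** Inputs from Statistical analyses: means 931 and 833 ms, SDs 42 and 123 ms, alpha 0.00625 (= 0.05/8), power 0.80. Two-sided testing is assumed, as sidedness is not stated.
- Difference: 931 − 833 = 98 ms.
- Common SD: √[(42² + 123²)/2] = √8446.5 = 91.9 ms.
- n per group = 2 × SD² × (z₁₋α/₂ + z₀.₈₀)² / difference² = 2 × 8446.5 × (2.734 + 0.842)² / 98² ≈ 22.5, so 23. The t-based version gives 25.

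The stated 24 is reproduced to within the method of calculation.

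**2. Reserve.** 48 = 2 × 24, so there is none. If incomplete children were dropped, t-based power on these inputs would be:

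| Complete children per group | Power |
|---|---|
| 24 | 0.79 |
| 22 | 0.74 |
| 20 | 0.68 |
| 18 | 0.61 |

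These figures are for a two-group comparison of overall reaction time, the only quantity for which the article gives SDs. They illustrate the missing reserve; they are not the power of the group-by-position test.

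**3. Completed blocks unused.** The plan has 48 × 3 = 144 blocks. If a share p of the children stop after two blocks, 48 × p × 2 completed blocks are discarded: about 5 at p = 5% (4.8) and about 19 at p = 20% (19.2). The range for p is an assumption.

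**4. Bias in the group gap, by simulation.** All settings are assumptions: 24 per group, random position order, between-child SD 50 ms, residual SD 50 ms, true gap 20 ms. Only preterm children leave, before the last block, with log-odds of leaving that rise with a poor score in the first two blocks.

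| Preterm children lost, of 24 | Log-odds slope per SD | Mean complete-case gap |
|---|---|---|
| 4.3 | 0 | 20 ms |
| 1.2 | 1 | about 18 ms |
| 2.4 | 1 | about 15 ms |
| 4.3 | 0.5 | about 16 ms |
| 4.3 | 1 | about 12 ms |
| 4.3 | 2 | about 7 ms |

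A model fitted to all completed blocks stayed near 20 ms.

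A separate run on a standardised scale (within-child correlation 0.5, true gap 0, slope 1 per SD) moved the complete-case estimate from its full-data value by about −0.07 SD with 3.1 of 24 lost and −0.13 SD with 5.5 lost. With no link to score, the shift stayed within 0.01 SD. The mixed model stayed within 0.001 SD throughout.

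**5. Position contrast.** With a 20 ms position effect added, the completers' free-minus-seated contrast was biased by less than 0.4 ms, because the order is random. In 2 of the 6 orders a child who leaves before the last block has already done both seated and free. That is one third of leavers, or about 4.3/3 = 1.4 children in the heavier-loss scenario, so the loss of precision is small.

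**The case against.** The strongest reply is that the article never says an incomplete child is removed. A reader might infer this from the named method, but it is only how such ANOVAs usually run. Replacement or re-testing may be settled in a fuller document that is not shown. This stands, and it rules out calling the plan's text an error. It does not remove the point, because the analysis method is stated and is open to comment as a choice.

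Second, little in the article suggests many incomplete sessions. There is one visit. Blocks are stated to last under 3 min; the trial timings suggest about 4 min (48 × about 5 s = 240 s), and even then task time with practice is at most about 3 × 4 + 2 = 14 min. There are breaks, and practice comes with feedback. Children whose disabilities would prevent the test, or who have ADHD-type inattention, are excluded, and participants must be without learning difficulties. This also stands. Against it, a block can be lost without the child stopping: position compliance is checked block by block, and each cue condition has only 48/4 = 12 trials per block, of which only correct ones count.

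Third, a reader might infer that the gap would collapse, say from 20 to 8 ms. That takes about 4.3 of 24 preterm children leaving, no term child leaving, and a log-odds slope of between 1.5 and 2 per SD. The article gives no rate, gap or SD for component scores that would support such a scenario. The link from weak attention to a poor component score is itself assumed, since the scores are reaction-time differences. For alerting, the Background reports no term-preterm difference at about 8 years.

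Fourth, the mixed model's good performance is partly built in: leaving was generated from observed blocks, so missing-at-random held by construction.

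**Conclusion.** The point holds as a minor improvement to a stated method. The ANOVAs as described would, in usual practice, use only children with all three scores, and the sample has no margin for losing any.

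Bias in the term-versus-preterm level is conditional: it needs loss that is both related to the scores and more common in preterm children. Under the assumed SDs and a 20 ms gap at slope 1, it runs from about 2 ms (1 of 24 lost) to about 8 ms (4 of 24 lost), and it is nil if loss is unrelated to score. The within-child position contrast, which carries the study's main aim, is essentially unbiased and loses only a little precision.

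The documents do not support saying that the protocol removes incomplete children, that many are expected, or that the group comparison is in fact biased.

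**What to change.** Fit each attention component with a linear mixed model (REML) with group, position and group × position as fixed effects, and either a random effect for child or an unstructured 3 × 3 within-child covariance. Include every completed block from every child who starts. Report the number of completed blocks by group and position. Keep the mixed ANOVA on children with all three blocks as a sensitivity analysis.

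The cost is a change of analysis wording, with no extra children or measurements. With complete data, the random-intercept form gives the planned tests, provided the estimated between-child variance is positive. The downside is reliance on missing-at-random given the completed blocks. That may fail for a block abandoned midway or judged unusable, so reasons for missing blocks are worth recording.

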## Discussion

The consequences of child mobility during learning are a recurrent concern for parents and teachers. In general, a behavior with a high level of mobility is perceived as the expression of a lack of concentration, and consequently a lack of performance. This study will reassess the contribution of mobility expression in specific attentional contexts that are usually present during fundamental learning in children aged 7-years.

Numerous findings suggest that mobility is not always a source of distraction [39, 46–49]. The work of Stoffregen’s team [48, 49] suggests that during the accomplishment of a supra-postural cognitive task such as calculating or memorizing, the organism may generate a spontaneous body sway to facilitate the performance of the associated supra-postural task. The modulation of self-generated body motions may correspond to unintentional attempts to increase arousal. This would be enabled by the increase in physiological parameters leading to greater cerebral activation, hence facilitating information processing [40, 50–52]. This heuristic assumption results from the U-inverted model of Yerkes and Dodson [53], which proposes a progressive improvement in cognitive performance with a moderate increase in the arousal level until reaching a threshold of this energetic solicitation, when the cognitive performance progressively decreases.

Furthermore, the behavioral strategies in children, especially their mobility, should be considered in the analysis of their difficulties during class time. In other words, we speculate that the spontaneous mobility often observed in school children may reflect a behavioral strategy when he/she is engaged in learning activities with attentional overload. This possible reassessment of child mobility has potentially important implications for educational practices in order to facilitate the attentional performance in children. A new pedagogical format of teaching could be proposed, taking into account the child’s mobility. Also, new pedagogical tools that allow the child to have free mobility could be designed such as stand-biased school desks [41–44]. Simple environmental changes in classrooms could enhance children’s cognitive functioning, driving their cognitive development and impacting educational outcomes. This could significantly improve learning abilities in children who were born preterm. These children are known to have poor or delayed development levels of attention. From the outcomes of this trial, educational innovations may be developed to help improve the adaptation to primary school in vulnerable children.
